# A mobile app using therapeutic exercise and education for self-management in patients with hand rheumatoid arthritis: a randomized controlled trial protocol

**DOI:** 10.1186/s13063-020-04713-4

**Published:** 2020-09-10

**Keywords:** Education, E-health, Exercise therapy, Mobile applications, Protocol, Randomized controlled trial, Rheumatoid arthritis, Self-management, Tele-rehabilitation

## Abstract

**Background:**

Therapeutic exercise is a safe and cost-effective approach to alleviate hand rheumatoid arthritis (RA)-related symptoms. This study aims to investigate the differences in self-management between a smartphone app (CareHand), using hand exercises and educational advices, compared with a standard approach, on hand overall function, pain intensity, stiffness, and grip and pinch strength in patients with hand RA.

**Methods:**

The project is a prospective, longitudinal, superiority, randomized controlled trial. Fifty-eight participants with hand RA will be randomly assigned into an experimental group (CareHand app) or a control group (conventional treatment). Control intervention involves a paper sheet with exercises and recommendations, and the experimental group includes the use of a smartphone app, which provides individualized exercise programs, self-management, and educational strategies to promote adherence to treatment. Both intervention protocols will last for 3 months. The principal investigator will conduct an educational session at baseline for all participants. Primary outcome comprises the overall hand function, assessed with the Michigan Hand Outcome Questionnaire (MHQ). Secondary outcomes include self-reported functional ability with the Quick DASH questionnaire, self-reported pain intensity and morning stiffness using a Visual Analogue Scale (VAS), and hand grip and pinch strength (dynamometer). Outcome measures will be collected at baseline, and at 1 month and 3-month follow-up.

**Discussion:**

This study will evaluate the effectiveness of a tele-rehabilitation tool, which uses exercise and self-management strategies, compared to a conventional approach, in patients with hand RA. The smartphone app will allow to monitor the patient’s status and to enhance patient-therapist communication. Some limitations may be related to the short follow-up duration and the lack of evaluation of psychosocial factors. Overall, this new way of promoting long-term effects in patients with a chronic rheumatic disease could be feasible and easy to implement in daily life clinical practice and current musculoskeletal care.

**Trial registration:**

ClinicalTrials.gov NCT04263974. Registered on 7 March 2020. Date of last update 15 April 2020. Ethics committee code: PI_RH_2018.

## Administrative information

Note: the numbers in curly brackets in this protocol refer to SPIRIT checklist item numbers. The order of the items has been modified to group similar items (see http://www.equator-network.org/reporting-guidelines/spirit-2013-statement-defining-standard-protocol-items-for-clinical-trials/).

## Introduction

### Background and rationale {6a}

Rheumatoid arthritis (RA) is a chronic autoimmune disease [1] and the most common inflammatory polyarthritis [2]. Overall, the prevalence rate of RA is about 1.1% of the adult population in Europe and North America [3], with lower occurrence in Mediterranean countries, e.g., 0.5% in Spain [4]. The exact cause of AR is unknown, although genetic, epigenetic, and environmental conditions may contribute to its development [1, 5], and help to explain the high variability in geographic presentation.

Up to 90% of patients with RA report wrist or hand problems, especially metacarpophalangeal (MCP) and proximal interphalangeal (PIP) joints [6], with symptoms such as pain, swelling, decreased mobility [7], loss of muscle mass [8], hand deformities, reduced strength [9], and stiffness [10], which causes impaired function and social participation [11]. This leads to a huge socioeconomic burden, higher than that of other non-communicable diseases [12], with an estimated annual loss of productivity of 11.500$ per person [13], and an increased 50% risk of unemployment [14].

The clinical management of hand RA includes pharmacological and non-pharmacological treatments that aim to prevent or control joint damage and RA-related disability, especially overall hand function and pain [15, 16]. The target of currently available medication for RA, e.g., non-steroidal anti-inflammatory drugs, glucocorticoids, and disease-modifying antirheumatic drugs (DMARDs), is remission or low disease activity [17], and to reduce hand symptoms and deformities [18]. However, the use of these drugs increases the direct healthcare costs by 300% [19]; hence, the cost-effectiveness of this approach is controversial [17]. In addition, muscle function is not always directly improved even when the disease is controlled [18]. Among non-pharmacological interventions, hand exercise programs are safe and cost-effective to alleviate symptoms in patients with RA [12] and may even enhance the effects of medication [20]. Therapeutic exercise for RA has demonstrated to be positive for hand function, although uncertainty remains about its impact on pain and strength [16]. Yet, there is evidence of a low rate of adherence to prescribed exercises in people with upper limb conditions [21]. Further studies of high methodological quality with hand function as the main outcome and the use of strategies to increase adherence are warranted [16].

Several approaches to improve adherence and compliance to treatment have been formerly proposed, e.g., promoting self-efficacy with exercises, clarifying and solving the main barriers to physical activity, using an exercise diary with pictures and explanations, establishing feasible objectives along with verbal and written contracting [18], monitoring patients with  phone calls [22], and raising awareness of the associated risks and benefits of a concrete health behavior [23]. It has been suggested that the use of smartphone applications has a great potential to achieve these goals [18]. In fact, the combination of smartphone apps with healthcare professionals’ intervention to promote self-management may improve adherence, participation, and long-term efficacy [24–26]. Technology implantation has a key role in current practice for the control and treatment of RA, and to enhance patients’ satisfaction and general wellness [26].

CareHand is an app specifically aimed at providing home exercise programs and educational advices about RA and pain management for patients with hand RA. This app records patients’ symptoms and exercise progression to adjust the therapeutic program, which helps to increase self-management [26], and participation and compliance to the treatment protocol [11]. The app has been developed by and under the supervision of different healthcare professionals, e.g., physicians, physiotherapists, and occupational therapists, to follow the current evidence-based guidelines for the treatment of patients with hand osteoarthritis or RA.

## Objectives {7}

The aim of this project is to investigate the differences in self-management using a smartphone app (CareHand), consisting of hand exercises and educational advices, compared with a standard approach (home exercise program on paper), on hand overall function, self-reported pain intensity and stiffness, and grip and pinch strength in patients with hand RA.

We hypothesize that the use of the smartphone app, compared to the exercise program on paper, can provide greater positive impact on hand function, pain, stiffness, and strength, immediately after the intervention protocol and in a 3-month follow-up.

## Trial design {8}

A single-blinded, parallel, two-arm group randomized, controlled, superiority trial will be conducted. The random sequence, with a 1:1 allocation of participants in the study groups, has been generated using an external website. The outcome data will be collected from a paper form or via telephone by a research assistant who is blinded to the treatment arm. The study protocol received the approval of the Research Ethics Committee of Virgen del Rocio and Virgen Macarena University Hospitals, Seville, Spain (code number: PI_RH_2018), and has been registered in ClinicalTrials.gov with registration number NCT04263974. Figure 1 lists the flowchart of the study design.

**Fig. 1 Fig1:**
[figure not shown]
CONSORT flow diagram template

## Methods: participants, interventions, and outcomes

### Study setting {9}

Eligible participants will be selected from the database of the Northern Seville and Aljarafe District, Andalusian Health Service, Seville, Spain. Recruitment, data collection, and educational sessions will be conducted at two community health centers located in Camas and Sanlúcar la Mayor, both villages in the Seville province, Spain. Data collection training will be carried out at the University of Seville (Faculty of Medicine and Faculty of Nursing, Physiotherapy and Podiatry). The list of study sites is available in the trial registration information.

### Eligibility criteria {10}

Adults with a confirmed rheumatic diagnosis of RA for more than 2 years, affecting a minimum of one wrist, MCP, or PIP joints, will be assessed for eligibility. RA is defined following the diagnostic criteria of the American College of Rheumatology [4, 27]. Participants will have to show at least 4 out of 7 of the following signs or symptoms: (a) morning stiffness at or around hand joints and/or wrist for more than 1 h during 6 weeks or more; (b) three or more actively swollen joints during 6 weeks or more; (c) swollen wrist, MCP, or PIP joints; (d) asymmetrical joint swelling; (e) radiographic evidence of erosion or decalcification at hand or wrist; (f) presence of rheumatoid nodules; and (g) positive rheumatoid factor. Participants will have to self-report pain in their hands and/or wrists, and decrease ability to carry out daily life activities involving the hands [28]. In addition, participants must have a smartphone or tablet with internet access. Exclusion criteria are as follows: (a) previous history of hand surgery or fracture in the 6 months before data collection [28], (b) waiting list for upper limb surgery [20], (c) having received intramuscular or intraarticular steroid injections within 4 weeks [23], (d) pregnancy [2], and (e) a moderate or severe cognitive impairment [9]. Participants will be told not to be involved in other manual therapy interventions during the study period.

### Who will take informed consent? {26a}

A researcher team member will obtain verbal and written informed consents from all patients during the baseline assessment. Participants will be clearly informed of the study aims, and potential risks or benefits, and that they can withdraw the study at any point with no need to provide any specific reason for that. All participants will be assigned a study identification code linked to their personal information, which will be stored in a protected database accessible only to one researcher.

### Additional consent provisions for collection and use of participant data and biological specimens {26b}

On the consent form, participants will be asked if they agree to the use of their data should they choose to withdraw from the trial. This trial does not involve collecting biological specimens for storage.

## Interventions

### Explanation for the choice of comparators {6b}

The so-called conventional intervention is the standard treatment protocol used in the Andalusian Public Health System for self-management in patients with hand RA. The exercises are listed in a paper sheet and consist of upper limb stretching and strengthening exercises, with greater focus on hand joints and wrist.

### Intervention description {11a}

Participants assigned to the control group will receive the usual care provided by the Andalusian Public Health System in Primary Care during 3 months. First, the principal investigator will conduct an educational session explaining the intervention details and including motivational messages to encourage participants to carry out their treatment protocol. Then, the exercise program and recommendations are delivered in a paper sheet. Pictures of mobility and stretching exercises are present in this paper, focused on fingers, hand, wrist, and elbow joints. A written explanation of how to perform the exercises, and the number of sets and repetitions are included. Patients will carry out the protocol four times per week during 15–20 min each session.

Participants randomly assigned to the experimental group will use the CareHand app. First, the principal investigator will give an educational session explaining how to manage the CareHand app and its main features, along with a motivational speech to encourage participants. Then, each individual will receive a unique code and password to log into the app and to start working with their smartphones. The CareHand app includes an exercise protocol focused on mobility, stretching, and strengthening of the hands, as well as educational advices, and strategies to promote self-management. Exercises included are automatically adapted on a daily basis according to the patient condition and evolution, and are provided with a detailed explanation included in the application. Pain intensity using a Visual Analogue Scale (VAS) will be assessed before and after the exercise program, and other self-reported outcome questionnaires will be collected once a week with the app. Participants will be asked to use the app four times per week, during 15–20 min each session, for 3 months. The app also includes information related to the disease; self-management strategies for pain, fatigue, and daily live activities; dietary advices; and benefits of performing regular physical activity. The CareHand app records the adherence to treatment, which will be automatically sent to a research member by e-mail. Figure 2 includes several images of the app main menu and an example of one of the exercises listed in the app.

**Fig. 2 Fig2:**
[figure not shown]
The CareHand application

Participants in both groups will receive a follow-up phone call from a research collaborator (RC) at weeks 1 (t1), 3 (t2), 5 (t4), 9 (t5), and 13 (t6) to promote adherence and to solve any problems or doubts that participants may have. Outcome measures will be collected at baseline (t0), and at 1 month (t3) and 3 months (t7) from baseline. Data collection at 1 month (t3) will be conducted by a phone call, and the rest of the assessments will be carried out at the same public health center where participants were initially recruited.

### Criteria for discontinuing or modifying allocated interventions {11b}

Any possible participants’ requests for discontinuing with the intervention or the follow-up will be considered, and no explanations will be asked for. Participants will be also informed that they cannot be involved in a manual therapy treatment through the study process. Medical treatment modification or worsening disease will not be a reason to discontinue the intervention and the follow-up, but all this information will be registered.

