### Provisions for post-trial care {30}

Hand exercise programs are safe. In patients with RA, no adverse effects have been attributed to self-management with hand exercises [16]. Hence, no harm or adverse effects are expected from trial participation. Nonetheless, participants will be asked to report any possible side adverse effect.

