### Adverse event reporting and harms {22}

Adverse events that may occur during the trial period will be self-reported by patients. The researchers supervising the interventions and those researchers collecting outcome measures at follow-up appointments will be also told to identify possible adverse events.

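### Staff will not ask why a participant stops the programme or the follow-up, so stops caused by an adverse effect or worsening disease cannot be systematically classified and may be under-recorded

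*Protocol article*

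**What the plan says.** All references are to the protocol article.

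- **Criteria for discontinuing or modifying allocated interventions {11b}.** Participants' "requests for discontinuing with the intervention or the follow-up will be considered, and no explanations will be asked for". The rule covers both stopping the programme and leaving follow-up. The same section says that a change in medical treatment or a worsening of disease "will not be a reason to discontinue the intervention and the follow-up, but all this information will be registered".
- **Who will take informed consent? {26a}.** Participants are told that "they can withdraw the study at any point with no need to provide any specific reason for that".
- **Provisions for post-trial care {30}.** Harm is not expected, but "participants will be asked to report any possible side adverse effect".
- **Adverse event reporting and harms {22}.** "Adverse events that may occur during the trial period will be self-reported by patients". Researchers supervising the interventions are also to look for events, and "those researchers collecting outcome measures at follow-up appointments will be also told to identify possible adverse events".
- **Intervention description {11a}, text after Fig. 2.** Both groups are called at weeks 1, 3, 5, 9 and 13 "to promote adherence and to solve any problems or doubts that participants may have".

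No section describes another way of recording why a participant stopped.

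**The concern.** The consent section gives a right not to answer. Section {11b} adds a rule not to ask. Protecting the participant needs only the first.

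The rule sits awkwardly with the protocol's own aims. Adverse effects are to be reported and looked for, and worsening disease is to be registered. Yet a request to stop is a contact at which such an event may well be the cause, and there staff are told not to enquire. Someone who leaves because the exercises made the hands hurt more may then look the same in the record as someone who leaves for lack of time.

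Two things are at stake:

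- **Harms.** There is no data monitoring committee, on the expectation that nothing beyond passing soreness will occur (section {21a}). Unexplained stops make that expectation harder to test.
- **Missing outcomes.** The section on non-adherence and missing data {20c} accepts that abandonment cannot be separated out and relies on intention-to-treat. Judging whether a missing 3-month Michigan Hand Outcome Questionnaire score is related to outcome is harder when the reason for leaving is unknown.

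**Working it through.** The point rests on how the sections fit together, and the plan gives no figure of its own to reproduce. The check has two parts.

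**1. Which routes would catch a harm-related stop?**

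- *Participant stops the exercises only.* Section {11b} names intervention and follow-up separately, so this person can stay in follow-up. Pain is rated at 1 and 3 months (Secondary outcomes), and the assessor check in {22} still applies. An adverse effect can be found, but nothing links it to the decision to stop.
- *Participant leaves follow-up.* The assessor check in {22} takes place at follow-up appointments, which this person misses. What remains:
  - Self-report ({22}, {30}) depends on the participant raising the event.
  - The calls are meant for adherence, retention and solving problems ({11a}, {11c}, {18b}). Harm may surface in them, but they are not described as adverse-event checks, and the article does not say that they continue after someone leaves.
  - Registration of worsening disease ({11b}) requires staff to learn of it.
- *Difference between arms.* Pain before and after exercise is described only for the app group ({11a}). A stop in the paper group may leave less trace, so under-recording could differ by arm.

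The gap is therefore concentrated in people who leave follow-up and have not mentioned a harm at any earlier contact. For them the error runs towards fewer recorded harms.

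**2. How large could it be?**

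Inputs from Sample size {14}: 58 participants, 24 per group needed to complete, 10% dropout. Allocation is 1:1 (Trial design {8}).

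- Per arm: 58 / 2 = 29.
- Expected stops: 0.10 × 58 = 5.8, about 6 in all, or about 3 per arm (0.10 × 29 = 2.9).
- Losses the sample size can absorb: 58 − 2 × 24 = 10.

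The share of stops caused by harm is an assumption, since the document gives none. For k harm-related stops in one arm and none in the other, with 29 per arm, the two-sided Fisher exact p is 2 × C(29,k) / C(58,k):

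| k, all in one arm | Rate in that arm | p against 0/29 |
|---|---|---|
| 0 | 0% | 1.0 |
| 3 | 3/29 = 10.3% | 2 × 3,654 / 30,856 = 0.24 |
| 6 | 6/29 = 20.7% | 2 × 475,020 / 40,475,358 = 0.023 |

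The last row is the extreme case at the planned dropout: every stop is due to harm, all fall in one arm, and none is reported by any route. The first row is no bias at all. The document does not say where between them the trial would fall.

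**The case against.** The strongest case on the other side is that harm collection does not depend on a withdrawal reason. Worsening disease and treatment changes are registered under the same section {11b}, adverse events have their own routes in {22} and {30}, both groups receive five calls, and nobody who stops is exempted from any of these. The clause in {11b} may simply repeat the consent right, and it does not forbid noting a reason that is volunteered. The article also condenses a fuller protocol, where the fields of a discontinuation form would normally be found.

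Much of this stands, and it rules out three stronger inferences:

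- *That harm-related stops cannot be counted.* Some can: those that are volunteered, surface in a call, or occur in someone who stays in follow-up.
- *That the harm result is biased towards none.* The article defines no harm endpoint and no comparison of harms between arms, and bias is possible but not shown.
- *That unexplained stops use up the trial's precision on harm.* No events in 29 fully observed participants gives a one-sided 95% upper limit of 1 − 0.05^(1/29) = 9.8%, close to 3/29 = 10.3%. This sets a hypothetical count beside a confidence bound; it gives a sense of scale and proves nothing about the data.

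Two parts do not stand. The clause is a stated procedure, so condensation does not explain it: the detail is present, and it says that staff will not ask. And reading it as a repeat of the consent right does not supply what is missing, a way of recording why someone stopped.

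**Conclusion.** The concern holds in limited form. As written, {11b} prevents systematic classification of stops by cause. Harm-related stops may be under-recorded, most likely towards fewer harms and mainly among those who leave follow-up; the other routes reduce the gap without closing it.

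About 6 participants would be exposed at the planned dropout, and up to 10 if the full allowance were used. The number harmed among them is unknown. This rests on a literal reading of the clause and on the article showing every route for recording a reason. No effect on the primary comparison is demonstrated; for that comparison the loss is in the ability to judge why outcomes are missing.

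**What to change.** In {11b}, replace the clause with wording such as: participants may stop the programme or the follow-up at any time without giving a reason; they will be invited, voluntarily, to say whether an adverse effect, worsening disease, a treatment change or another reason was involved.

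Record the answer, or that it was declined, by arm and separately for stopping the programme and leaving follow-up. Report it with the harms and the participant flow. For anyone who stopped before the change, record that the reason was not sought, so that this is not confused with declining.

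**Cost:** one sentence and one form field. The consent right in {26a} is untouched and no clinical rule changes. Some participants will decline, so classification will remain incomplete. Under the section on protocol amendments {25}, the change must be reviewed by the ethics committee. The Trial status section describes recruitment as ongoing, so on that footing the change could still serve later participants.
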